#### 2.6.1. Measures

All study outcome measures, collected at baseline, 2 and 6 months, are listed in Table 4.

The primary clinical study outcome, A1C, will be measured using A1cNow+, the National Glycohemoglobin Standardization Program Certified, which is a CLIA-waived system that uses a finger stick test. The American Diabetes Association considers this clinical measure an indication of success for diabetes self-management. A1C assessments will be assessed by a clinical staff. They will occur in private community locations at 2 sites.

The secondary study outcome, medication adherence, will be assessed using a self-reported medication adherence scale, the 3-item Extent of Nonadherence domain in the reliable and validated DOSE-Nonadherence survey. This measure screens for nonadherence and is calculated by computing the mean of the 3 items (score range is 1–5). Participants with mean scores of 3 (i.e., scoring “1” on each of the 3 items) will be classified as nonadherent, while participants with mean scores >3 will be classified as adherent [46,47].

Other outcomes: Several validated measures will provide data on the effect of proposed theoretical constructs on Peers EXCEL and its impact on the patient-specific psychosocial constructs. These measures are listed in Table 4.

Demographic/clinical factors include age, gender, self-reported health, depressive symptoms, self-reported cardiovascular event, hospitalization, emergency room visit due to diabetes complications, and number of prescription medications used.

Feasibility and acceptability outcomes: Outcomes to be evaluated will include recruiting of ambassadors, HLWD and Peers EXCEL participants, attrition, and participation in program components. We will record how many participants were screened to meet recruitment goals, document which recruitment goals strategies work best, and the length of time needed to recruit. We will also document the number of participants who attended each group sessions, and the number of participants who continued their participation in the intervention will be compared with the numbers we recruited at the beginning. For participants in the intervention arm, phone use will be tracked weekly by asking participants the amount of time they spent on the phone with their ambassador.

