### 2.4. Participants

There are four groups of individuals involved in the pilot trial, but data analyses, and intervention outcomes will be collected principally from the HLWD and Peers EXCEL participants, i.e.,:

HLWD participants (control arm) (n = 12) –those who receive the HLWD content—who are African Americans with uncontrolled type 2 diabetes and nonadherent to their medicines.

Peers EXCEL participants (intervention arm) (n = 12)—those who receive the Peers EXCEL content—who are African Americans with uncontrolled type 2 diabetes and nonadherent to their medicines.

HLWD and Peers EXCEL participants’ inclusion criteria include: (1) Adults who are aged between 18 and 90 years old who are African American/Black with type 2 diabetes, and can speak and/or read English, (2) Self-report they have been prescribed at least one oral or injectable diabetes medicine, (3) Will be located in in the area geographically during the study period, (4) Self-reported medication nonadherence on the DOSE Nonadherence scale and (5) Most recent A1c value is ≥7.5% based on information collected by the research team at point of care A1C testing.

Exclusion criteria include: (1) If currently participating in a diabetes management or program focused on medication adherence, (2) Self-reported, schizophrenia, dementia, and untreated bipolar disorder or active substance use disorder (not having been in recovery for three or more months) (3) Older adults who report experiencing severe hypoglycemia in the past, and required medical assistance or the administration of glucagon

We will elicit feedback from individuals serving as Ambassadors and HLWD facilitators:

Peers EXCEL ambassadors (n = 4)—that is, those who relay intervention content via phone—who are African Americans with controlled diabetes (A1C ≤ 7.5%) and are adherent to their medication. Other inclusion criteria include (1) Adults who are aged between 18 and 90 years old who are African American/Black with type 2 diabetes, and can speak and/or read English, (2) Self-report they have been prescribed at least one oral or injectable diabetes medicine, (3) Being diagnosed with type 2 diabetes for at least one year (4) Will be located in the area geographically during the time of the study, (5) Being able to support another peer and track the phone conversations, and (6) Being prepared to attend all meetings and sessions focused on training them for their roles

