### 2.7. Data Analysis

Quantitative. Paired *t*-tests (or a non-parametric corresponding test such as Wilcoxon rank sum test) will examine pre- vs. post-intervention changes in participant’s A1C, medication adherence, and other psychosocial outcomes across groups to examine a signal of change. We will use descriptive statistics to calculate ambassadors’ feasibility measures, HLWD and Peers EXCEL participants, including ambassador recruitment, ambassador attrition, and extent of ambassador participation in sessions related to their training and intervention. We will consider the recruitment approach as feasible if: there is recruitment of all ambassadors and participants as planned, attrition for both ambassadors and participants is less than or equal to 10%, and the rate for ambassador and participant participation is equal to or higher than 80%.Qualitative. Interviews and focus groups will be audio-recorded and transcribed. Research assistants will code transcripts inductively using NVivo v 12 and conduct qualitative content analysis [56]. Qualitative content analysis will be used to organize the themes. All transcribed transcripts will be read initially for data immersion, taking time to read all the data line by line. Then, the codes and themes will be developed and organized with a conceptualization of how the themes are all lined together in the data. We will compare all themes exploring if there are similarities, interconnections, and/or differences across all themes. We will continue all data analysis until we get to theoretical and there are no more new dimensions in the data [57,58,59]. We will establish rigor of the data and explore the trustworthiness of the data analysis process using Lincoln and Guba (1985) four general criteria [60]. These are credibility, transferability, dependability, and confirmability. For credibility, two research assistants will code the transcripts independently—investigator triangulation (i.e., multiple coders involved in the data analysis), discuss similarities and divergences, and reach agreement by consensus before the final data interpretation. We will member check with participants interested in being part of the process to confirm if our interpretation is salient/credible—to check for resonance with participant experiences. Confirmability, objectivity/potential congruence between researchers. To ensure our findings are based on our participants’ responses and not any personal motivations or personal bias from our research team, after coding, all similarities and divergences will be discussed. Agreement will be reached on codes before results interpretation. Transferability, the scope to which results are applicable to other contexts. We will purposively sample individuals with varied intervention experiences and use detailed descriptions to show how the research study’s findings may be applicable in other contexts, circumstances, and situations. Dependability—the ability to achieve consistent findings if the study is done as described. We will create and report a detailed audit trail of our process throughout the analysis process. Documents and field notes data will also be analyzed using content analysis.Mixed. After analyzing the quantitative and qualitative data separately, the mean score differences, statistical effect sizes, and themes will be compared in the context of the feasibility, acceptability, and primary and secondary outcomes. The results from both phases will be interpreted together in a joint display to aid a meta-inference of the merged results.

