## Figures and Tables

**Figure 1 pharmacy-11-00002-f001:**
[figure not shown]
The Randomization Process.

**Table 1 pharmacy-11-00002-t001:** Intervention Content for Intervention Arm (Peers EXCEL) and Control Arm (HLWD).

Intervention Content	Weeks											
	1	2	3	4	5	6	7	8	9	14	19	24
Group sessions of beliefs about diabetes, provider mistrust and pharmacist communication	*	*										
Group sessions of diabetes self-management, healthy eating, problem solving, exercise, communication, medication, cultural experiences, discussing diabetes with family			*	*	*	*	*	*				
			#	#	#	#	#	#				
Referral to community health worker, if requested									*	*	*	*
									#	#	#	#
Peer-based phone call support									*	*	*	*

* Intervention Arm (Peers EXCEL Program); # Control Arm (Healthy Living with Diabetes Program).

**Table 4 pharmacy-11-00002-t004:** Measures for Study Outcomes.

Construct	Measure	Baseline	2 Months	6 Months
Primary Clinical Outcome				
Blood glucose	Hemoglobin A1c (A1C)	×	×	×
Secondary Study Outcome				
Medication adherence	DOSE-Nonadherence survey [46,47], extent of nonadherence domain	×	×	×
Other Measures				
Diabetes-health beliefs	Brief Illness Perception Questionnaire [48]	×	×	×
Beliefs about diabetes medicines	Beliefs about Medicines Questionnaire [35]	×	×	×
Diabetes and medication self-efficacy	Diabetes Empowerment Scale—Short Form [49] Self-Efficacy for Adherence to Medication Use Scale [50]	×	×	×
Diabetes distress	Diabetes Distress Scale (DDS-2) [51]			
Patient-provider communication	Patient’s Perceived Involvement in Care Scale [52]	×	×	×
Patient activation	Patient Activation Measure [53]	×	×	×

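### The DOSE-Nonadherence cut-off contradicts the score definition: 1 on each of three items gives a mean of 1, not 3, and the labels are probably reversed

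*Protocol article*

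**What the plan says.** Section 2.6.1 (Measures) names the secondary outcome instrument as "the 3-item Extent of Nonadherence domain in the reliable and validated DOSE-Nonadherence survey". It describes the scoring as "This measure screens for nonadherence and is calculated by computing the mean of the 3 items (score range is 1–5"). The classification rule follows directly: "Participants with mean scores of 3 (i.e., scoring “1” on each of the 3 items) will be classified as nonadherent". The same sentence then defines the other class: "while participants with mean scores >3 will be classified as adherent".

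The same scale is used in two places:

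- **Eligibility.** Inclusion criterion 4 in section 2.4 (Participants) reads "Self-reported medication nonadherence on the DOSE Nonadherence scale". It gives no cut-off of its own.
- **Secondary outcome.** Table 4 lists "DOSE-Nonadherence survey [46,47], extent of nonadherence domain" at baseline, 2 months and 6 months. Section 2.7 (Data Analysis) says that paired t-tests or a non-parametric counterpart "will examine pre- vs. post-intervention changes in participant’s A1C, medication adherence, and other psychosocial outcomes across groups". It does not say whether the 1–5 score or the adherent/nonadherent class is analysed.

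The article gives no item wording, response anchors or statement of reverse coding for this scale, and no second cut-off.

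**The concern.** The sentence that sets the cut-off disagrees with the sentence that defines the score. Someone scoring a form from this text cannot tell whether 3 is a mean or a sum, and the choice decides who counts as nonadherent.

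The labels also appear to run against the construct. A domain called Extent of Nonadherence would be expected to rise with nonadherence, yet the rule attaches the adherent label to the higher scores.

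Two things depend on this rule. It is the only threshold in the document by which criterion 4 could be applied at screening. It is also the only guide to which direction of change on the secondary outcome is favourable. With 12 participants per arm, a few people wrongly admitted or labelled would matter to a pilot whose signal is meant to inform a larger trial.

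**Working it through.** **Inputs (section 2.6.1).** Three items; score is their mean; score range 1–5; nonadherent if the mean is 3, explained as 1 on each item; adherent if the mean is above 3. I assume that each item takes the whole values 1 to 5, which fits the stated range.

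**Step 1: the plan's own figure.** The plan says that three answers of 1 give a mean of 3.

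- Mean: (1 + 1 + 1) / 3 = 1, the floor of the stated range. Not reproduced.
- Sum: 1 + 1 + 1 = 3. Reproduced, but a sum runs from 3 to 15, not from 1 to 5.

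**Step 2: the rule read as a mean.** There are 5 × 5 × 5 = 125 response patterns. A mean of 3 is a sum of 9, reached by the orderings of (1,3,5), (1,4,4), (2,2,5), (2,3,4) and (3,3,3): 6 + 3 + 3 + 6 + 1 = 19. Replacing each answer x by 6 − x swaps sums above and below 9, so each side holds (125 − 19) / 2 = 53 patterns.

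**Step 3: the rule read as a sum.** Only (1,1,1) sums to 3. The remaining 125 − 1 = 124 patterns exceed 3, and no sum falls below 3.

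| Reading of 3 | Nonadherent | Adherent | No class |
|---|---|---|---|
| Mean | 19 | 53 | 53 |
| Sum | 1 | 124 | 0 |

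**Step 4: do the readings agree?** The 19 patterns that are nonadherent under the mean reading are all adherent under the sum reading. The pattern (1,1,1), which the rule itself cites as nonadherent, gets no class under the mean reading. So no pattern is nonadherent under both. The readings agree only on the 53 patterns with a mean above 3.

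**Step 5: direction.** The pattern (5,5,5) has mean 5 and sum 15, so it is adherent under both readings. If the labels instead followed the domain name on the sum scale, (1,1,1) would be adherent and the other 124 nonadherent, the opposite of the printed sum rule for all 125 patterns.

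The patterns are counted with equal weight to show the logic of the rule. They are not expected patient frequencies and do not say how many of the 24 participants would be affected.

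**The case against.** The mean/sum contradiction has no good defence. It is a rule stated wrongly rather than a detail left to another document. The other side is stronger on what follows from it.

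- **Direction.** A reader might infer that reversal is proved. It is not. The article shows no anchors and states no coding, and section 2.6.1 also calls the instrument a medication adherence scale. If the items were reverse-coded, the direction could be right. The domain name makes reversal the likelier reading, but only the cited instrument can settle it. The mean/sum contradiction would remain either way.
- **Combining the harms.** It is tempting to say that the rule both leaves low scorers unclassified and enrols people at the floor of the scale. These belong to different readings: the first needs 3 to be a mean, the second needs it to be a sum. They cannot occur together.
- **Outcome analysis.** A reader might conclude that the secondary outcome will be misclassified. The tests in section 2.7 suit the 1–5 score, and nothing says that the binary class is analysed. If the score is used, the computed change is unaffected by the cut-off, and only the interpretation of its sign is at risk.
- **Eligibility.** Criterion 4 names the scale without a threshold, and the study's screening form may carry the correct key. The link is still reasonable, because section 2.6.1 says the measure screens for nonadherence and gives the only threshold. Actual wrong enrolment is not shown.

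All four limits stand, and they make the consequences conditional.

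**Conclusion.** The point holds in this form. It is certain from section 2.6.1 alone that the cut-off does not follow from the score definition: the stated item answers give a mean of 1, and only their sum is 3. The rule is therefore unusable as printed. It yields 19 nonadherent, 53 adherent and 53 unclassified patterns on one reading, and 1 and 124 on the other.

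It is probable, but not confirmed, that the labels are also reversed. This rests on the domain name and on the absence of any stated reverse coding.

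The consequences are conditional. If staff apply the printed rule to criterion 4, the wrong people could be enrolled. Under the sum reading, everyone who qualified would be at the lowest possible score, and their later scores could only stay there or rise. If higher scores mean more nonadherence and the printed labels guide interpretation, worsening could be reported as improvement. The documents do not support a claim that either has happened or must happen. The correction is still needed, because this is the only operational definition given for an entry criterion and for the secondary outcome's classes.

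**What to change.** 1. Check the item anchors and the scoring key of the cited instrument before rewording anything.
2. Restate the rule on one scale, mean or sum, with a cut-off that assigns every possible score to a class and a plain statement of which direction means more nonadherence.
3. If, and only if, the anchors confirm that higher means more nonadherence, the rule becomes: mean = 1 (sum = 3) adherent; mean above 1 (sum above 3) nonadherent.
4. Refer to that same rule in inclusion criterion 4, and check that the screening form uses it.
5. State in section 2.7 that the 1–5 mean is the analysed secondary outcome, and which direction of change counts as improvement.

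The cost is a corrected scoring sentence, a cross-reference, one line in the analysis section and a check of the screening form's key. No extra data are needed.

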#### 2.6.2. Mixed Methods Integration

Qualitative and quantitative data from multiple sources will be integrated to allow for meta-inferences about the feasibility of conducting a future large-scale effectiveness randomized controlled trial. Sources of quantitative data will include study administrative records (to assess feasibility of recruitment, intervention adherence, and retention); surveys completed after each session (to assess acceptability of different features of the intervention, including the presenter/HLWD facilitator, content, structure, and group session logistics); and surveys completed at the post-intervention assessment (to assess acceptability and adherence to data collection procedures and overall intervention acceptability). Qualitative data on acceptability of data collection will also be obtained by the open-ended questions in the post-intervention semi-structured interviews and document review. To obtain qualitative data on the other four feasibility domains of greatest interest—recruitment, intervention acceptability, intervention adherence, and retention—we will hold semi-structured interviews within two weeks following the final HLWD group session (scheduled to take place after all participant assessments) and at the end of the 6-month intervention. We will also evaluate documents and field notes data from study team calls with participants (to explore reasons for declining participation related to recruitment and retention). We will employ various strategies for integrating quantitative and qualitative outcomes. Qualitative data may provide insight into reasons why corresponding quantitative metrics are lagging or provide convergent and contextualized evidence in support of positive quantitative metrics.

#### 2.6.3. Intervention Fidelity

Evaluating content fidelity involves determining whether content will be delivered as intended. Study team members will use a 14-item program monitoring tool to assess the HLWD facilitator content fidelity in 5 areas: Environment (e.g., room and seating for the group session), Content (e.g., time used for the presentation and clarity of content), Presenter, Program Delivery, and Methods/Materials (e.g., educational strategies used). An external evaluator will address things such as the facilitators’ adherence to the program guide, how they assisted in participants’ problem-solving and brainstorming activities, assigning of homework, and helping participants develop action plans to promote self-efficacy [54,55]. Peers EXCEL group sessions fidelity will focus on delivery of culturally tailored content.

For the Peers EXCEL arm, we will also monitor fidelity similar to the process used in prior studies [22,23,43]: (1) group education sessions with participants will be audio-recorded to examine intervention implementation, (2) phone calls every week from program assistants to ambassadors to discuss content and rate of phone calls with peer participants, and (3) bi-weekly calls from program assistants to document how the peer phone calls are going. All group sessions will be audio recorded to avoid a Hawthorne effect, where knowing they are being recorded for certain sessions enhances the facilitators’ actions during that session. We will then listen to a randomly chosen set of sessions. The PI, study coordinator, program assistant, and the facilitators will assess for fidelity by discussing the sessions and creating an opportunity to provide feedback on each session.

### 2.7. Data Analysis

Quantitative. Paired *t*-tests (or a non-parametric corresponding test such as Wilcoxon rank sum test) will examine pre- vs. post-intervention changes in participant’s A1C, medication adherence, and other psychosocial outcomes across groups to examine a signal of change. We will use descriptive statistics to calculate ambassadors’ feasibility measures, HLWD and Peers EXCEL participants, including ambassador recruitment, ambassador attrition, and extent of ambassador participation in sessions related to their training and intervention. We will consider the recruitment approach as feasible if: there is recruitment of all ambassadors and participants as planned, attrition for both ambassadors and participants is less than or equal to 10%, and the rate for ambassador and participant participation is equal to or higher than 80%.Qualitative. Interviews and focus groups will be audio-recorded and transcribed. Research assistants will code transcripts inductively using NVivo v 12 and conduct qualitative content analysis [56]. Qualitative content analysis will be used to organize the themes. All transcribed transcripts will be read initially for data immersion, taking time to read all the data line by line. Then, the codes and themes will be developed and organized with a conceptualization of how the themes are all lined together in the data. We will compare all themes exploring if there are similarities, interconnections, and/or differences across all themes. We will continue all data analysis until we get to theoretical and there are no more new dimensions in the data [57,58,59]. We will establish rigor of the data and explore the trustworthiness of the data analysis process using Lincoln and Guba (1985) four general criteria [60]. These are credibility, transferability, dependability, and confirmability. For credibility, two research assistants will code the transcripts independently—investigator triangulation (i.e., multiple coders involved in the data analysis), discuss similarities and divergences, and reach agreement by consensus before the final data interpretation. We will member check with participants interested in being part of the process to confirm if our interpretation is salient/credible—to check for resonance with participant experiences. Confirmability, objectivity/potential congruence between researchers. To ensure our findings are based on our participants’ responses and not any personal motivations or personal bias from our research team, after coding, all similarities and divergences will be discussed. Agreement will be reached on codes before results interpretation. Transferability, the scope to which results are applicable to other contexts. We will purposively sample individuals with varied intervention experiences and use detailed descriptions to show how the research study’s findings may be applicable in other contexts, circumstances, and situations. Dependability—the ability to achieve consistent findings if the study is done as described. We will create and report a detailed audit trail of our process throughout the analysis process. Documents and field notes data will also be analyzed using content analysis.Mixed. After analyzing the quantitative and qualitative data separately, the mean score differences, statistical effect sizes, and themes will be compared in the context of the feasibility, acceptability, and primary and secondary outcomes. The results from both phases will be interpreted together in a joint display to aid a meta-inference of the merged results.

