Peers EXCEL provides an adapted diabetes self-management program for African Americans which includes group education sessions and one on one peer support. Group education includes the addition of new sessions that address misperceptions about diabetes and medicines influenced by racial discrimination/mistrust of providers, building self-efficacy, and provider communication. The additional one-on-one peer support occurs through race-congruent phone follow-up from other African Americans called Ambassadors. *Ambassadors* are African Americans with diabetes who are adherent to their medicines paired with African Americans with diabetes who are nonadherent (*Buddies*). Ambassadors’ interactions with their buddies focuses on addressing medicine and diabetes misperceptions, sharing experiences managing diabetes and medicines, and supporting self-efficacy and self-advocacy with their healthcare providers [31]. In the pilot trial of Peers EXCEL that examined feasibility and acceptability, we found the rates of recruitment were 80% for buddies and 100% for ambassadors. The rate at which the primary outcomes, medication adherence and A1C were retained was 75%. Participants mean completion rate was 13.4/17 of group sessions and phone calls with their ambassadors. About 84% of intervention phone calls were completed between the ambassadors and their buddies. We found no statistically significant differences in mean A1C and medication adherence. However, we found a clinically meaningful reduction (−0.7) in mean A1C at the inference point, 6-month follow up compared to the baseline. Based on the qualitative themes, participants reported the program to be culturally appropriate and acceptable with a perception of improved communication with their provider. They also reported that they learned strategies to assist with goal setting, and developed the confidence and motivation they needed for self-management [23].

Given these results, our next step is to conduct a pilot randomized controlled trial (RCT) of Peers EXCEL compared to HLWD to examine the feasibility and acceptability of the intervention and protocol and explore the benefits of the intervention in African Americans with uncontrolled diabetes using mixed methods.

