## 2. Materials and Methods

### 2.1. Study Objectives and Design

The study objective is to evaluate the feasibility and acceptability of the trial protocol and the exploratory benefit of Peers EXCEL compared to HLWD using a pilot randomized controlled intervention mixed methods trial, among African Americans with uncontrolled diabetes. We will randomize participants to receive either Peers EXCEL or HLWD only. All individuals who agree to participate will be assigned a number and allocated to either the Peers EXCEL or HLWD group using computer-generated random numbers. The randomization process is illustrated in Figure 1. The study duration will be December 2022 until September 2023.

Our study aims are to:(1)Evaluate if the intervention and protocol are feasible and acceptable. We will investigate if Peers EXCEL would be feasible to implement and be acceptable to African Americans with uncontrolled type 2 diabetes. Qualitative and quantitative data from multiple sources will be integrated to allow for meta-inferences about the feasibility of conducting a future large-scale effectiveness RCT.(2)Pilot test Peers EXCEL to examine its effect in improving A1C and medication adherence. We hypothesize a signal of change in mean hemoglobin A1c that is clinically meaningful (≥0.6 reduction) for participants randomized to Peers EXCEL compared to participants randomized to HLWD at baseline, 2 months, and 6 months. We expect to see an improvement in medication adherence, assessed via self-report in the Peers EXCEL participants compared to the HLWD participants at 6 months.

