### 2.6. Data Collection

Quantitative data will be collected using in-person surveys at baseline, 2 months, and 6 months. Qualitative interviews and focus groups will be conducted with all study participants, HLWD facilitators, and the ambassadors to understand their experiences with the intervention and their feedback on the program. These interviews will be conducted at 2 and 6 months. Field notes and documents from program assistants will be reviewed for data abstraction.

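### The non-parametric fallback for the paired t-test is named as the Wilcoxon rank sum test, which is for independent samples; the paired counterpart is the Wilcoxon signed-rank test

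*Protocol article*

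**What the plan says.** Section 2.7 (Data Analysis) gives one sentence on inference for the quantitative outcomes: "Paired *t*-tests (or a non-parametric corresponding test such as Wilcoxon rank sum test) will examine pre- vs. post-intervention changes". It goes on to list A1C, medication adherence and "other psychosocial outcomes across groups to examine a signal of change". The parenthesis, "or a non-parametric corresponding test such as Wilcoxon rank sum test", holds the only non-parametric test named, and the signed-rank test appears nowhere.

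The data are repeated measures on the same people. Section 2.6 says "Quantitative data will be collected using in-person surveys at baseline, 2 months, and 6 months", and section 2.6.1 and Table 4 put A1C and the adherence score on the same schedule. Section 2.4 plans 12 participants in each arm.

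Two changes in A1C appear in the article. Section 2.1 hypothesises a change that is "clinically meaningful (≥0.6 reduction) for participants randomized to Peers EXCEL compared to participants randomized to HLWD". The Introduction reports of the earlier pilot that "we found a clinically meaningful reduction (−0.7) in mean A1C at the inference point, 6-month follow up compared to the baseline". No SD, pre-post correlation, significance level or power is given.

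**The concern.** The sentence pairs a parametric test with a rank test and calls the second the counterpart of the first. They are not counterparts. The paired t-test and the signed-rank test both work on within-person differences. The rank sum (Mann-Whitney) test ranks two sets of values as if they came from different people.

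If an analyst judged the paired t-test unsuitable and followed the text, twelve pre values and twelve post values from the same twelve people would be treated as 24 unrelated observations. The p-value would be miscalibrated, and with positively correlated measurements it would be too large. This sentence is the only inferential analysis stated for the primary clinical outcome and for the secondary one. The trial looks for a signal to carry into a larger trial, so a test that mutes within-person change works against its purpose.

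**Working it through.** **No figure to reproduce.** The article states no power or error rate for this analysis. What can be checked is which way the named test errs, and by how much under stated assumptions.

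**Direction.** Let σ be the SD at each visit, r the pre-post correlation and n the number of people.
- True variance of the mean change: 2σ²(1 − r)/n.
- Variance if the two visits are treated as independent: 2σ²/n.
- The standard error is therefore too large by a factor of about 1/√(1 − r).

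As a rough normal approximation, a nominal 5% two-sided test then needs a correctly scaled statistic of 1.96/√(1 − r):
- r = 0.3: 1.96/√0.7 = 2.34, actual error about 1.9%.
- r = 0.5: 1.96/√0.5 = 2.77, actual error about 0.6%.

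The test is conservative for any positive r, and more so as r rises.

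**Simulation inputs.**
- From the article: n = 12 (one arm) or 24 (both arms pooled). The change of 0.6 is stated for a between-arm contrast and is used here only as an illustrative within-person change. The change of 0.7 is the earlier pilot's.
- Assumed: bivariate normal data, SD 1.0 to 2.0, r from 0 to 0.9, two-sided 5%.
- 8,000 replicates per setting. The signed-rank test is exact; the rank sum test is exact for n = 12 and asymptotic for n = 24.

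**Actual type I error, n = 12, nominal 5%**

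| r | Rank sum | Signed-rank |
|---|---|---|
| 0 | 4.6% | 4.3% |
| 0.3 | 2.0% | 4.0% |
| 0.5 | 0.9% | 3.9% |
| 0.7 | 0.2% | 4.4% |
| 0.8 | about 0.1% | 3.8% |
| 0.9 | <0.1% | 3.9% |

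**Power, n = 12, change 0.6, SD 1.5**

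| r | Rank sum | Signed-rank | Share of power lost |
|---|---|---|---|
| 0.3 | 10% | 16% | 37% |
| 0.5 | 8% | 22% | 64% |
| 0.7 | 5% | 33% | 85% |
| 0.8 | 3% | 47% | 93% |
| 0.9 | 2% | 76% | 97% |

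Share lost = 1 − (rank sum power / signed-rank power), from unrounded rates; for example, at r = 0.5, 1 − 0.079/0.221 = 0.64. At r = 0 nothing is lost.

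**How the loss moves with the assumptions (change 0.6)**

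| n | SD | r = 0.3 | r = 0.5 | r = 0.7 | r = 0.9 |
|---|---|---|---|---|---|
| 12 | 1.0 | 29% | 54% | 74% | 85% |
| 12 | 2.0 | 43% | 70% | 89% | 99% |
| 24 | 1.0 | 22% | 35% | 45% | 43% |
| 24 | 1.5 | 34% | 58% | 77% | 92% |

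With a change of 0.7, n = 12 and SD 1.5, the pattern is the same: 14% against 21% at r = 0.3, 11% against 28% at r = 0.5, and 6% against 59% at r = 0.8.

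**The other reading.** If the rank sum test is meant for change scores between arms (12 against 12, difference 0.6, SD 1.5 at each visit), it is a valid test. Its power is then about 14% at r = 0.5, 21% at r = 0.7 and 51% at r = 0.9.

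**The case against.** Four points deserve weight.

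First, the wording is permissive. The rank sum test is offered as an example, and a signed-rank test would satisfy the requirement that the test correspond to the paired t-test. The error may be a slip of one word. But the only example given is the wrong one, so an analyst who follows it goes astray.

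Second, *across groups* may point to a comparison between arms, and the hypotheses in sections 2.1 and 3 are between-arm. A rank sum test of change scores would be sound there. It would then be the counterpart of a two-sample t-test, not of the paired t-test in the sentence. On either reading the sentence needs correcting.

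Third, a reader might infer that the fallback would throw away most of the power. The article does not support that as a general statement. It depends on an SD and a correlation that the article does not give; at r of about 0.3, or with all 24 pooled and SD 1.0, less than half is lost. Nor does the article show that the fallback is likely to be used: the paired t-test leads, and there are no distributional data and no rule for switching. The simulation also uses normal data, where a fallback would hardly be needed, so it illustrates the cost of ignoring pairing rather than forecasting this trial.

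Fourth, the consequences are contained. The feasibility criteria (recruitment, attrition, participation) do not use this test. The A1C signal is expressed as a mean reduction, and the mixed-methods step uses mean differences and effect sizes, none of which depends on the fallback p-value. The error is conservative, so it does not inflate false signals. All of this stands and lowers the severity.

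**Conclusion.** The named test is wrong as written: for pre-post change in the same people, the counterpart of the paired t-test is the Wilcoxon signed-rank test. If the fallback were applied as named to pre and post values, it would be conservative at any positive correlation.

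For one arm of 12, with a change of 0.6 and SD 1.5 at a two-sided 5% level, actual type I error falls to about 2% at r = 0.3, 0.9% at r = 0.5 and roughly 0.1% or less at r of 0.8 and above. At the same three correlations, between about a third and nine-tenths of the signed-rank test's power is lost. With all 24 pooled and SD 1.0, the loss is 22% to 45% for r from 0.3 to 0.9. The SD, correlation, alpha and normality are assumptions.

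This is a correction worth making, but not a defect that must hold up the trial: it concerns a fallback test in a feasibility pilot that claims no power.

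**What to change.** In section 2.7, replace the rank sum test with the Wilcoxon signed-rank test as the alternative to the paired t-test for within-person pre-post change. State separately that any comparison of change scores between the two arms would use a two-sample t-test, with the rank sum test as its non-parametric counterpart, so that *across groups* has one meaning.

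The cost is a sentence of wording. Design, sample size, data collection and schedule are unaffected.
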